### Statistical methods

The study will be reported following the STROBE statement [42] and the SPIRIT-PRO Extension [43]. Descriptive statistics will be used to determine the prevalence of sexual dysfunction and fertility-related distress by diagnosis and sex. These will be presented as means and standard deviations and as percentages of participants above the described cut-offs for these outcomes. Prevalence rates in the cancer group will be compared to prevalence rates in the general population by sex and age group, using Students’ t-test and χ^2^ tests. To determine predictors for sexual dysfunction and fertility-related distress at each assessment we will perform logistic regression models for each primary outcome (SexFS v2-domains and RCAC-dimensions) for the whole group and by sex. Independent variables will include sex (whole group), partner status, parenthood status, child wish (only for RCAC), satisfaction with sex life pre-diagnosis (only for SexFS v2), diagnosis, treatment intensity, body image, anxiety, and depression. Trajectories of these issues over time (T1, T2 and T3) will be analyzed with linear mixed models. Relations between sexual dysfunction and fertility-related distress, and between these issues and our secondary outcomes, will be analyzed with Pearson’s correlation coefficients. Statistical analyses will be performed in collaboration with external statisticians.

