### Objectives

The primary objective of the present study is to determine the prevalence and predictors of sexual dysfunction and fertility-related distress following a cancer diagnosis in young adulthood compared to prevalence rates for the general population. Further aims are to investigate the trajectories of these issues over time, the co-existence between sexual dysfunction and fertility-related distress, and the relation between these issues and body image, anxiety and depression, health-related quality of life, self-efficacy related to sexuality and fertility, and fertility-related knowledge.

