### Eligibility criteria

#### Cancer group

The following inclusion criteria will be used: All individuals in Sweden in ages 18–39 who were diagnosed with brain tumor, breast cancer, cervical cancer, lymphoma, ovarian cancer, or testicular cancer between January 2016 and August 2017. Potential participants without valid address information will be excluded. Furthermore, approached individuals who on their own initiative inform us that they cannot complete the survey due to cognitive impairment, poor health or non-ability to read and/or understand Swedish will also be excluded.

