### Sample size

Based on official statistics on cancer incidence in Sweden [2, 40] the eligible population is estimated to approximately 1500 for the inclusion period. Based on our experience of moderate response rates (50–60%) in surveys on sensitive issues in this age group when no incentives were offered [7, 11], we expect the addition of incentives (2 cinema tickets) to result in a larger proportion of responders. An estimated response rate of 70% would result in 1050 participants at baseline. At baseline, a majority of participants (≈80%, *n* = 840) are expected to rate sexual dysfunction or fertility-distress meeting the inclusion criteria for the embedded RCT [23]. Of those invited to the RCT, about half are expected to consent participation (*N* = 420) and these will be excluded for further follow-up in the Fex-Can Cohort, leaving 630 participants for the longitudinal analyses. Attrition in the Fex-Can Cohort due to deaths and other reasons for non-response is estimated to 15% at following assessments, giving an estimated response rate at T2 (*n* = 535) and T3 (*n* = 454). Sample size determination was based on the recommendation to include at least 5 events of the dependent variable of interest (in this case: the primary outcome measures SexFS and RCAC) for each independent variable included in the multivariable logistic regression models [41]. Thus, we estimated that at least 50 events of the dependent variable in the sample are required in order to include up to ten independent variables. Based on the incidence rates of the selected diagnoses, we expected a distribution of approximately 65% women and 35% men in the eligible sample. Previous data of sexual dysfunction and fertility distress in the Swedish setting [7, 11] indicate that the number of events of the dependent variables at baseline is ≈30% for males and ≈60% for females. Based on these numbers, we estimate the sample size to be sufficient for determination of potential predictors for both sexes at all assessment occasions, including the 5-year follow-up. As the Fex-Can Cohort is an observational study, no formal power calculation was conducted.

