## Discussion

This population-based cohort study aims to determine the prevalence and predictors of sexual dysfunction and fertility-related distress in young adults diagnosed with cancer. The results of the study will increase understanding of the trajectories of sexual dysfunction and fertility-related distress over 5 years following diagnosis.

Our study design includes a large nationwide sample of young adults diagnosed with different cancers and will therefore establish prevalence rates of sexual dysfunction and fertility-related distress over the first 5 years after diagnosis. One of the selected diagnoses, brain tumors, is a cancer often excluded in this kind of research and the group’s sexual dysfunction and fertility-related distress is still largely unknown. Potential participants will be identified through National Quality Registers with excellent coverage, ensuring that all individuals in the age group diagnosed with the selected cancers will be approached [44]. The design also allows for analyses of non-responders and attrition including highly reliable clinical variables. At the baseline assessment some patients may still be on treatment (e.g. lymphoma and breast cancers) and others will have finished their treatment (e.g. testicular cancer). Therefore, treatment status will be described in detail for each diagnosis when reporting prevalence at baseline, and all models will control for current treatment status. While most of the selected patient-reported outcome measures are standardized instruments, it should be noted that the study-specific measures, as well as the shortened versions of the BIS and RCAC for the comparison group, have not been validated. With a young adult comparison group assessed with the same standardized measures it will be possible to determine to what extent the self-rated problems are related to being treated for cancer. As the prevalence of sexual dysfunction in women and men has been reported to vary between countries [45, 46], the use of a comparison group randomized from the total general population in the country is a strength. However, the fact that the comparison group is only assessed at one time point is a limitation as it does not allow comparison of trajectories of these issues over time.

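### Baseline prevalence is planned as a crude percentage of responders; registry-weighted figures beside it, and a fixed eligible denominator, would be a cheap improvement

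*Protocol article*

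**What the plan says.** All references are to the protocol article.

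- Objectives: "The primary objective of the present study is to determine the prevalence and predictors of sexual dysfunction and fertility-related distress", in comparison with the general population.
- Statistical methods: "Descriptive statistics will be used to determine the prevalence of sexual dysfunction and fertility-related distress by diagnosis and sex". Results are given as means and standard deviations and "as percentages of participants above the described cut-offs for these outcomes". The comparison with the general population is by sex and age group; diagnosis is not named as a stratifier there. No weighting or other non-response adjustment is stated.
- Sample size: "the eligible population is estimated to approximately 1500 for the inclusion period", and "An estimated response rate of 70% would result in 1050 participants at baseline". The authors' earlier experience was of "moderate response rates (50–60%) in surveys on sensitive issues in this age group when no incentives were offered".
- Eligibility criteria, cancer group: the exclusions cover "approached individuals who on their own initiative inform us that they cannot complete the survey due to cognitive impairment, poor health" or insufficient Swedish. The comparison group has the same rule.
- Discussion: "The design also allows for analyses of non-responders and attrition including highly reliable clinical variables". The same section says that the study will settle prevalence over the five years after diagnosis.
- Registry data section: the clinical items include stage, treatment type and relapse. Age and sex are not on that list, but age must be known to apply the eligibility criteria.

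**The concern.** A percentage of responders estimates prevalence among all eligible patients only if responders and non-responders have the same prevalence within each reported group. In a survey on sex and fertility, willingness to answer may well depend on age, stage, treatment and diagnosis. The Discussion makes a population claim and points to the data that could partly support it, yet the methods section stops at the crude percentage.

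The eligibility rule adds a second weakness. Two equally ill invitees are classified differently depending on whether they contact the study: one is excluded, the other is a non-responder. The reported response rate then depends on that contact. The cognitive-impairment clause could matter most for brain tumours, a group the Discussion highlights as seldom studied, although the document gives no figure for this.

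**Working it through.** **Inputs from the document (Sample size):** eligible N = 1500; response r = 0.70; 65% women, 35% men; expected prevalence about 60% in women and 30% in men; earlier response 50–60%.

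**The plan's own figures.** 1500 × 0.70 = 1050. 1050 × 0.80 = 840 meet the RCT criteria; half of these, 420, enter the RCT; 1050 − 420 = 630 remain. 630 × 0.85 = 535.5 (stated 535) and 535 × 0.85 = 454.75 (stated 454). The chain reproduces.

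**Sampling error at baseline.** Half-width = 1.96 × √(p(1 − p)/n).
- Women: n = 1050 × 0.65 = 682.5; 1.96 × √(0.6 × 0.4/682.5) = 3.7 points.
- Men: n = 1050 × 0.35 = 367.5; 1.96 × √(0.3 × 0.7/367.5) = 4.7 points.

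These are for each sex with diagnoses pooled. Figures by diagnosis will be less precise.

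**Shift from non-response.** True prevalence = r·p(resp) + (1 − r)·p(non), so true minus reported = (1 − r) × d, where d = p(non) − p(resp). The document gives no value for d, so a range is assumed:

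| d (assumed) | Shift at r = 0.70 | Women, reported 60% | Men, reported 30% |
|---|---|---|---|
| −30 | −9 | 51% | 21% |
| −20 | −6 | 54% | 24% |
| −10 | −3 | 57% | 27% |
| +10 | +3 | 63% | 33% |
| +20 | +6 | 66% | 36% |
| +30 | +9 | 69% | 39% |

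At 50–60% response, each 10 points of d would move prevalence by 4–5 points. At 70% the shift equals the half-width when d is 3.7/0.30 ≈ 12 points (women) or 4.7/0.30 ≈ 16 points (men). If none or all of the non-responders were affected, the bounds are 0.7 × 60% = 42% to 42% + 30% = 72% for women, and 21% to 51% for men.

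**What weighting can remove.** The table shows total non-response error. Weights remove only the part explained by the weighting variables, which cannot be computed from the document. An illustration of pooling over one known variable: if 75% of women and 60.7% of men responded (assumed, averaging 70%), the crude pooled figure would be (0.65 × 0.75 × 60% + 0.35 × 0.607 × 30%)/0.70 = 50.9%, against a true 0.65 × 60% + 0.35 × 30% = 49.5%. Weighting on that variable would remove 1.4 points.

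**Denominator.** Holding 1050 responders fixed and removing 75 people (5%, assumed) gives 1050/1425 = 73.7%. Removing 2% gives 71.4% and 10% gives 77.8%. The crude prevalence does not change, because those removed gave no answers.

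**Later assessments.** The 420 who leave for the RCT are selected on the baseline outcome. On the plan's figures, the share of the longitudinal group with a qualifying problem at baseline falls from 840/1050 = 80% to (840 − 420)/630 = 66.7% by this removal alone. Weights built only from registry variables do not use the scores on which this selection was made.

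**The case against.** The strongest reply is that the text never says unweighted, that an article condenses a fuller plan, and that weights and intervals are often left to an analysis plan. That has force: an unseen plan may already contain weights. But the article does state the estimator and whose percentage it is, and the eligibility rule is a protocol matter that an analysis plan would not repair.

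Second, reporting by diagnosis and sex already removes distortion from differing response across those two factors in those tables. This stands. What remains is stage, treatment and age within those groups, and diagnosis mix in the general-population comparison, which is by sex and age group.

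Third, registry variables are clinical and say nothing about partner status, education or interest in the topic, so the gain may be small. This also stands, and is a reason to show both figures.

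Fourth, low response and attrition bias are acknowledged in the Discussion and met with incentives and several ways of answering; reminders are also planned. These may raise response but do not adjust for what is lost.

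A reader might infer that reported prevalence will be 6 to 9 points too high. Those figures follow only from assuming 60% in responders and 40% in non-responders, at 70% and 55% response. The document supports neither the contrast nor its direction, and the lower response rate comes from surveys without incentives. A reader might also infer that registry data are reserved for describing non-response, or that exclusions will go unreported. The Discussion says only what the design permits, and nothing rules out adjustment or a count of exclusions.

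**Conclusion.** The point holds as a cheap improvement to a stated method. No figure in the plan is wrong. Part of the primary objective rests on a crude responder percentage while 30% non-response is expected and data for a partial correction are said to exist. Its possible size is 3 points of prevalence per 10-point difference at 70% response, with the difference assumed and its sign unknown. That is comparable with the sampling error for each sex once the difference reaches about 12 points (women) or 16 points (men). The share that registry weights would remove is unknown.

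The exclusion rule affects the stated response rate, not the crude prevalence. It would be tempting to extend the same weights to the 3- and 5-year data, but the plan's own figures do not support that: about 420 of 1050 leave after selection on the baseline outcome.

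**What to change.** - **Statistical methods:** report baseline prevalence with response-propensity or calibration weights on registry age, sex, diagnosis, stage and treatment, beside the crude percentages and both with 95% CIs. Use the weighted figures in the comparison with the general population. State that weighting corrects only the part of non-response that registry variables explain.
- **Eligibility criteria, cancer group:** count approached people who report being too ill or cognitively impaired to answer as eligible non-responders. Nobody is asked to answer who cannot; only the denominator changes.
- **3- and 5-year assessments:** do not carry the registry-only weights forward. Any weights there must also include the baseline outcome scores and RCT entry.

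The cost is some analysis work on data already planned, slightly wider intervals and a slightly lower stated response rate.

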#### Comparison group

A random sample of 2000 young adults (1000 women and 1000 men) will be drawn from the Swedish population register (SPAR) and approached regarding study participation. The survey will be sent to potential participants, together with a letter with information about the study including the voluntary nature of participation. As for the cancer group, it will be possible to complete the survey on paper, via the web or telephone, and two reminders will be sent to non-responders. The comparison group will be offered the same incentive for participation as the cancer group i.e., two cinema tickets. The comparison group will only be assessed once.

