##### Sexual function

The Patient-Reported Outcomes Measurement Information System© Sexual Function and Satisfaction Measure version 2 (SexFS v2) is a measure assessing sexual function and satisfaction in men and women regardless of sexual orientation [26]. Items in the SexFS v2 are scored on a five-point scale (ranging from 1 = None/Not at all to 5 = Very/A lot). In this study four specific domains for women will be included: Vaginal lubrication, Vaginal discomfort, Vulvar discomfort – clitoral, and Vulvar discomfort – labial. For males, the specific domain Erectile function till be used. Additionally, four gender-neutral domains will be included for all participants: Interest in sexual activity, Orgasm – ability, Orgasm – pleasure, and Satisfaction with sex life. Item response theory is used to calculate domain scores, which are transformed to a T-score metric where 50 represents the mean for sexually active American adults (standard deviation = 10) [26]. The SexFS v2 has shown adequate content, construct and known-groups validity as well as test-retest reliability [26, 27]. The selected items and domains of the SexFS v2 were translated into Swedish and linguistically validated in accordance with the procedure developed by FACITrans and PROMIS [28].

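### Student's pooled t-test is named for the mean-score comparisons although group sizes must differ in at least one sex; if variances also differ its level shifts, and Welch's test removes this at almost no cost

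*Protocol article*

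**What the plan says.** The Statistical methods section announces means with standard deviations and percentages beyond cut-offs, then a comparison of the cancer group with the general population "by sex and age group, using Students’ t-test" and χ² tests. A t-test applies to means, so the natural reading is t-test for mean scores and χ² for percentages. Nothing is said about equal variances, a variance check or Welch's form.

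The group sizes come from two places. Under Sample size: "An estimated response rate of 70% would result in 1050 participants at baseline", and "we expected a distribution of approximately 65% women and 35% men in the eligible sample". Under Recruitment, Comparison group: "A random sample of 2000 young adults (1000 women and 1000 men". That last figure counts people approached, not people who reply.

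The only standard deviation for a primary outcome belongs to the SexFS reference metric, where "50 represents the mean for sexually active American adults (standard deviation = 10". It describes neither study group.

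**The concern.** Student's test uses one pooled variance for both groups. Its standard error is right when the two variances are equal, and nearly right when the group sizes are equal. When both differ, the test is too liberal if the smaller group is the more variable one, and too conservative if the larger group is.

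Unequal sizes are built into this design: a cancer group split about 65:35 by sex is set against a comparison group drawn 50:50. Unequal variances are plausible but not shown. The cancer group pools six diagnoses, and the Discussion notes that some patients will still be on treatment at baseline while others will have finished; differences in mean between such subgroups would widen the overall spread. At stake is the accuracy of the p-values for the mean-score comparisons, with an error that could differ between men and women.

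**Working it through.** **The plan's own figure.** 1500 eligible × 0.70 = 1050, as stated.

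**Cancer group by sex.** 1050 × 0.65 = 682.5 and 1050 × 0.35 = 367.5, taken as 682 women and 368 men. The split is stated for the eligible sample; carrying it to responders assumes equal response by sex.

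**Comparison group by sex.** The article gives no response rate for this group. Assumed: 40% to 70%, the same in both sexes, which gives 400 to 700 per sex.

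**Are the sizes unequal?** With a common response rate p, each sex has 1000p comparators. This cannot equal both 682 and 368. At 70% women are nearly balanced (682 vs 700) and men are not (368 vs 700). At 40% men are nearly balanced (368 vs 400) and women are not (682 vs 400). Balance in both sexes would need about 68% response in women and 37% in men.

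**Further assumptions.** SD 12 in patients and 9 or 10 in comparators (ratio 1.33 or 1.2); two-sided 5% level, since the article states none.

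**Formula** (large sample; group 1 = cancer, group 2 = comparison):

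- Pooled variance: V = [(n1 − 1)σ1² + (n2 − 1)σ2²] / (n1 + n2 − 2)
- SE used by the test: √[V(1/n1 + 1/n2)]
- True SE: √(σ1²/n1 + σ2²/n2)
- True level = 2 × [1 − Φ(1.96 × SE used / true SE)]

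**Two worked cases, SD 12 vs 9.**

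- Men, 368 vs 700: V = 102.69, SE used 0.6525, true SE 0.7121, ratio 0.916, level 7.25%.
- Women, 682 vs 400: V = 120.73, SE used 0.6920, true SE 0.6432, ratio 1.076, level 3.50%.

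**True level of a nominal 5% pooled test:**

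| Comparators per sex | Men (368), SD 12/9 | Men, SD 12/10 | Women (682), SD 12/9 | Women, SD 12/10 |
|---|---|---|---|---|
| 400 | 5.27% | 5.17% | 3.50% | 3.99% |
| 500 | 6.04% | 5.65% | 4.07% | 4.39% |
| 600 | 6.69% | 6.05% | 4.60% | 4.74% |
| 700 | 7.25% | 6.39% | 5.08% | 5.05% |

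**Sensitivity to the SD assumption.** With equal SDs the level is 5.00% at any sizes. With the SDs reversed (9 in patients, 12 in comparators), men at 368 vs 700 have 3.24% and women at 682 vs 400 have 6.85%.

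**Does Welch's test repair it?** In simulations with normal data (20,000 replicates per scenario; sizes 682/500, 368/500, 368/700, 102/250 and 580/250, the last two being illustrative age bands; SD ratios 1.0, 1.2 and 1.5), Welch's level was 4.8% to 5.5% throughout. With equal SDs and power near 80%, the largest loss against Student's test was at 368/700: 79.73% vs 79.57%, or about 0.2 points.

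**The case against.** The strongest reply is that the article contains no error here. It gives no SDs, no comparison-group response rate, no age bands and no significance level, so there is no stated error rate to contradict. With equal variances the test is exact whatever the sizes, and if patients were less variable the direction would flip. The choice between the pooled and the Welch form is often left to the analysis plan, and Student's may be meant loosely. All of this stands, and it makes the point conditional and minor. What it does not remove is that the article names a specific test, that the sizes cannot match in both sexes under similar comparator response, and that a test without the equal-variance assumption is available at almost no cost.

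Three stronger readings are tempting and are not supported:

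- **Distortion within age strata is established.** Splitting the women 20:80 over two bands with 275 comparators each gives 137 vs 275 and 546 vs 275, and levels of 7.45% and 3.15% at SD 12 vs 9. The split, the 275 and the SDs are all invented for the example; the article defines no bands.
- **The test is wrong in both directions.** That needs a stratum in which the more variable group is clearly the larger one. If patients are the more variable and 70% of comparators reply, the sex-level error is upward in men and almost nil in women (5.1%).
- **The t-test carries the primary comparison.** The primary objective is stated in terms of prevalence. Percentages fall to the χ² test, which this issue does not touch.

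**Conclusion.** The point holds as a conditional, low-severity improvement. Unequal sizes in at least one sex follow from the plan's own figures, provided comparator response is similar in men and women. Unequal variances are assumed. Given patients with SD 12 against comparators with 9 or 10, and 40% to 70% comparator response, the pooled test's true level is about 5.2% to 7.3% in men and 3.5% to 5.1% in women. At the milder ratio of 1.2 the whole range is about 4.0% to 6.4%. A reader might infer that the planned mean comparisons are invalid; the document does not support that, because its figures fix neither the size nor the direction of any distortion.

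**What to change.** In Statistical methods, replace Student's t-test by Welch's t-test for the comparisons of mean scores between the cancer and comparison groups. If these contrasts are fitted as regressions, use heteroscedasticity-robust standard errors. Leave the χ² tests as they are. It would help to say in the same sentence that the t-test is for mean scores and χ² for percentages, since the present wording attaches both to prevalence rates. The cost is one word in the plan and a software option; no data collection or sample size changes.

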### Setting

The diagnoses included in the Fex-Can Cohort are selected based on the diseases and/or treatments having potentially negative consequences on fertile ability or sexual life. The incidence of the selected diagnoses in Sweden in 2016 was: brain tumors (*n* = 153), breast cancer (*n* = 350), cervical cancer (*n* = 195), lymphoma (*n* = 132), ovarian cancer (*n* = 39), and testicular cancer (*n* = 220). Individuals diagnosed with leukemia were not included in the Fex-Can Cohort due to an ongoing study concerning fertility issues in this group. Participants will be identified via the Swedish National Quality Registers for Brain Tumors, Breast Cancer, Gynecological Oncology, Lymphoma, and Testicular Cancer. All individuals diagnosed with the selected diagnoses at ages 18–39 during a time period of 18 months will be approached regarding study participation. Data collection will be performed approximately 1.5 years after diagnosis (baseline assessment) and 3 and 5 years after diagnosis. At baseline most participants are expected to have completed first-line treatment and be in the phase of returning to work and studies. In order to time these data assessments to participants’ time of diagnosis, data collections will be performed in three waves (A-C), see Fig. 1. Data for the comparison group will be collected on one occasion.

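### The sex-specific follow-up models in men run at about 5 events per coefficient; Firth-penalised logistic regression would remove a modest inflation of the odds ratios at little cost

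*Protocol article*

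**What the plan says.** Under Statistical methods, the protocol article states that "we will perform logistic regression models for each primary outcome", where the primary outcomes are the individual SexFS domains and RCAC dimensions. The models are run for the whole group and by sex at each assessment. From the instruments described, that is 11 outcomes in men (5 domains, 6 dimensions) and 14 in women (8 and 6). The estimator is not named.

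In a men-only or women-only model the listed predictors are partner status, parenthood, child wish (RCAC) or pre-diagnosis satisfaction (SexFS), diagnosis, treatment intensity, body image, anxiety and depression: eight variables. The Discussion adds current treatment status to all models, making nine.

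The Sample size section rests on the advice to "include at least 5 events of the dependent variable of interest" per independent variable, hence 50 events for up to ten variables. It judges the sample sufficient for both sexes at every assessment, including 5 years. The expected numbers run from "An estimated response rate of 70% would result in 1050 participants at baseline" through "leaving 630 participants for the longitudinal analyses" to 535 and 454 at the two follow-ups. Diagnosis sizes are given under Setting.

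**The concern.** Maximum-likelihood log odds ratios are biased away from zero when there are few events per estimated coefficient, and they are infinite when a category contains no events or only events. The plan sizes itself on five events per variable, then splits by sex, follows a reduced cohort and includes diagnosis as a multi-level predictor. The thinnest models are therefore those in men at follow-up, and the thinnest category is ovarian cancer in women.

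Predictors are part of the primary objective. If the models are run by default maximum likelihood, the odds ratios for men at 3 and 5 years will on average be somewhat too large and noisier than they need be. If an ovarian contrast fails, the analyst would have to merge or drop categories after seeing the data.

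**Working it through.** **1. Reproducing the plan's numbers (Sample size).**
- 1500 × 0.70 = 1050 at baseline.
- 1050 × 0.80 = 840 eligible for the embedded trial; 840 × 0.50 = 420 leave; 1050 − 420 = 630.
- 630 × 0.85 = 535.5, stated as 535 (T2, 3 years); 535 × 0.85 = 454.75, stated as 454 (T3, 5 years).

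The plan's figures reproduce.

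**2. Events in men.** Inputs: 35% men and a 30% event rate. The rate is stated for baseline; carrying it to follow-up, and applying it to every outcome, is an assumption. The coefficient count is also an assumption, because coding is not given: nine variables, with diagnosis in three levels (brain, lymphoma, testicular) taking two coefficients and each other variable one, gives ten.

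| Assessment | Men | Events | Per variable (9) | Per coefficient (10) |
|---|---|---|---|---|
| Baseline | 1050 × 0.35 = 367.5 | 110 | 12.2 | 11.0 |
| T2 | 535 × 0.35 = 187 | 56.2 | 6.2 | 5.6 |
| T3 | 454 × 0.35 = 159 | 47.7 | 5.3 | 4.8 |

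The T3 count is just below the 50 that the section names for ten variables.

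Sensitivity (assumption): suppose every event case is eligible for the embedded trial, 80% of men are eligible, and half of those leave. The event rate among those remaining is then (30 − 15)/(100 − 40) = 25%. That gives 46.8 events at T2 (4.7 per coefficient) and 39.7 at T3 (4.0).

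**3. Women at T3.** 454 × 0.65 = 295. At the stated 60% rate the limiting count is the non-events, 295 × 0.40 = 118. With five diagnoses (four coefficients) there are 12 coefficients, so 118/12 = 9.8 each. Overall density is not the problem.

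Splitting the 2016 brain and lymphoma cases evenly by sex (an assumption), the female total is 76.5 + 66 + 350 + 195 + 39 = 726.5. Expected women at T3:
- ovarian 39/726.5 × 295 = 16
- lymphoma 66/726.5 × 295 = 27
- brain 76.5/726.5 × 295 = 31
- cervical 195/726.5 × 295 = 79
- breast 350/726.5 × 295 = 142

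Only the ovarian cell is very small.

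**4. Simulation of ML against Firth.** 3000 data sets per scenario, true odds ratios of about 1.35 to 2, correlated body image, anxiety and depression, and the diagnosis mix above.

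| Scenario | Mean bias of log OR, ML | Firth |
|---|---|---|
| Men T3, 30% events | +10.4% | +0.3% |
| Men T3, 25% | +10.7% | +0.1% |
| Men T2, 30% | +7.3% | −0.9% |
| Men T2, 25% | +9.0% | +0.1% |
| Men baseline, 30% | +3.7% | −0.3% |
| Women T3, 60% | +6.8% | 0.0% |

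For size: exp(1.104 × ln 2) = 2.15, so a true odds ratio of 2.0 in men at T3 is reported as about 2.15. Across separate set-ups with other assumed effects, the inflation in men was 7–10% at T2 and 10–11% at T3, and ML mean squared error was about 20–27% above Firth. Interval coverage for men at T3 was about 94–95% with ML and 95.5–96.5% with Firth. Wald power for an odds ratio of 2 in men at T3 was 43% with ML and 38% with Firth.

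**5. The ovarian contrast.** At 60% events, ML failed or separated in 0.5% of women's data sets at T3 and Firth in none. The ovarian log odds ratio was inflated by 15% with ML and 2% with Firth. If one domain had a rate near 15% (an assumed figure that the protocol does not give), ML broke down in about 6–13% of fits across set-ups. A direct check agrees in order of size: with 15.8 ovarian cases at a 15% rate, the chance of no event among them is 0.85^15.8 = 8%.

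**The case against.** The strongest reply is that the protocol nowhere says maximum likelihood. It says logistic regression, and a condensed article may leave the estimator to an analysis plan written with the external statisticians. That stands: the absence of a named small-sample method is not an error. The point survives as an improvement, because the stated models run in the ordinary way give measurably biased and noisier estimates, and a better estimator is available.

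The second reply is that the plan counts events per variable, and on that count T3 gives 47.7/9 = 5.3. That also stands. A reader might infer that the plan breaks its own rule of five; for nine variables it does not. The figure of 4.8 depends on a coding that the protocol leaves open. Nor do the documents support a density below five at both follow-ups: at the stated 30% rate T2 is 5.6, and it falls below five only under the assumed loss of event cases to the embedded trial.

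Third, the effect is small. A shift of about 10% on the log odds ratio is roughly 0.1–0.15 of a standard error, and ML coverage stays near 95%. This is correct and limits the weight of the point.

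For women, a reader might infer several very small diagnosis cells, or multiply a separation rate over the 14 outcomes to make failure look likely. Neither is supported. Only ovarian cancer is very small, the outcomes are correlated and share the same 16 or so women, and separation is rare at the only event rate the protocol gives.

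**Conclusion.** The point holds as a cheap improvement. In men, the follow-up models have about 5.6 (T2) and 4.8 (T3) events per coefficient, and default estimation would inflate log odds ratios by about 7–10% and 10–11%, with mean squared error about 20–27% above Firth. In women it concerns the ovarian contrast only: separation is under 1% at the stated 60% rate, and becomes material (about 6–13% of fits) only if a single domain has a rate near 15%.

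These figures rest on the baseline event rates holding at follow-up, on ten coefficients in men and twelve in women, on an even sex split for brain tumours and lymphoma, and on assumed effect sizes. They do not show that the planned analysis would mislead on which predictors matter. The larger limitation in men at 5 years is imprecision, with power for an odds ratio of 2 near 40% under either estimator.

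**What to change.** In Statistical methods, specify Firth-penalised logistic regression with profile penalised-likelihood confidence intervals for:
- the sex-specific models at 3 and 5 years; and
- any other model with fewer than 10 limiting events (the smaller of events and non-events) per coefficient, or with a diagnosis category holding fewer than 5 events or non-events.

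Baseline and whole-group models gain little and can stay as they are. The covariate list need not change, and no further data are required.

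The cost is one sentence, a method less familiar to clinical readers, odds ratios slightly closer to 1, and about 2–5 points of nominal power. It does not cure imprecision. When editing, the sponsor should also note in Sample size that the expected count for men at 5 years is about 48, just under the 50 named there for ten variables.
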